### Control (6 month reminder) group

Women in the control group will receive no text reminders for the first 6 months of the study period. A single text message reminder (same text as for intervention group) will be sent to these women at 6 months postpartum (measured from date of birth of baby).

### Primary study outcomes

Oral glucose tolerance test undertaken by 6 months postpartum

### Secondary study outcomes

Fasting blood glucose test undertaken by 6 months postpartum

Glycated haemoglobin (HbA1c) test undertaken by 6 months postpartum

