### Outcome data collection: 6 months postpartum

All women in the study will be asked to complete a questionnaire at 6 months after the birth of the baby either by post or by email (using Survey Monkey), depending on their expressed preference at trial entry, to ascertain whether an OGTT was undertaken within the first 6 months, or whether a fasting blood glucose or glycated haemoglobin (HbA1c) test was used instead. The questionnaire also asks for the date and results of these tests, where known. The date and results of the OGTT will be confirmed using the hospital clinical information system, or by contact with the participant’s general practitioner, where necessary. The questionnaire also examines women’s attitudes towards the OGTT, as well as reasons for not being able to undertake the test, if applicable. Where questionnaires are not returned within 2 weeks, participants will be contacted by telephone, and then again in another 2 weeks if the questionnaires are still not received by the study team. During this telephone contact, participants will be asked whether or not they have completed an OGTT within the six months since they gave birth.

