### Sample size

The baseline rate of OGTT uptake used in the sample size calculation for the proposed trial is 37%; this rate is at the lower end of the range in the recent review by Tovar and colleagues (2011) [17]. Using a figure from the lower end of this range is a sound estimate, given that the health centres in the study had reminder systems in place, and that some results came from surveys with moderately low response rates [17]. Data from the South Australian Gestational Diabetes Mellitus Recall Register indicates that the actual rate may be somewhere between 26 and 56 percent [25].

The Stata version 10.0 sample size calculator has been used to calculate the target sample size.

The figures entered were:

▪ baseline uptake of postnatal OGTT 37%

▪ projected 18% absolute improvement to 55% (48% relative increase)

▪ power 80%

▪ significance (two-tailed) 5%

This resulted in a calculation that the study will require 262 women (131 in each arm). With a predicted up to 5% loss to follow up, 276 women will be required.

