### Analyses and reporting of results

Baseline characteristics of all randomised women will be compared descriptively between the study groups. Outcome comparisons will be made according to the treatment allocation at randomisation on an ‘intention to treat’ basis. Categorical variables will be reported as risk ratios with corresponding 95% confidence intervals. Continuous outcomes will be reported as mean (and standard deviation) for normally distributed results, or median (interquartile range) for results which are not normally distributed. All model assumptions will be assessed. Statistical significance will be defined at the 0.05 level using a two-sided comparative test.

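### Both secondary outcomes are defined as any fasting glucose or HbA1c test by 6 months but collected as substitutes for an OGTT, and telephone follow-up names only the OGTT

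*Protocol article*

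**What the plan says.** Under Secondary study outcomes the protocol article lists two items: "Fasting blood glucose test undertaken by 6 months postpartum" and "Glycated haemoglobin (HbA1c) test undertaken by 6 months postpartum". Neither depends on whether the woman also had an OGTT.

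Under Outcome data collection: 6 months postpartum, the questionnaire is said to establish whether an OGTT was done, "or whether a fasting blood glucose or glycated haemoglobin (HbA1c) test was used instead". The section adds: "The questionnaire also asks for the date and results of these tests, where known". Confirmation through the hospital information system or the general practitioner is described for the date and results of the OGTT only. Women who do not return the form are telephoned, and in that call "participants will be asked whether or not they have completed an OGTT within the six months since they gave birth". No other test is named for the call.

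Under Analyses and reporting of results, "Categorical variables will be reported as risk ratios with corresponding 95% confidence intervals". The article does not say how a woman with both an OGTT and another test is counted, which direction of a secondary outcome is favourable, or how common the alternative tests are expected to be.

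**The concern.** A test that was done and a test done in place of an OGTT are different quantities. The first can occur in any randomised woman. The second can occur only in a woman who did not have the primary outcome event. The reminder is designed to increase OGTTs, so a working intervention shrinks the group in which a substitute test is possible.

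A trial that succeeds on its primary outcome could then report risk ratios below 1 for fasting glucose and HbA1c testing. A reader could take these as a reduction in testing, although nothing may have changed in how women without an OGTT were tested. It would also be hard to tell whether the reminder raised overall postpartum testing or moved women from one test to another.

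The second issue is ascertainment. As described, a woman reached only by telephone supplies the primary outcome but no information on either secondary test. Where the secondary tests are reported, they are not covered by the record check.

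**Working it through.** **The plan's own figure.** Inputs from Sample size: "baseline uptake of postnatal OGTT 37"%, rising to 55%; 80% power; two-sided 5%.

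- Without continuity correction, n per arm = [1.96 √(2 × 0.46 × 0.54) + 0.842 √(0.37 × 0.63 + 0.55 × 0.45)]² / 0.18² = 119.2, rounded up to 120.
- With continuity correction, n′ = (n/4) × [1 + √(1 + 4/(n × 0.18))]² = 130.03, rounded up to 131 per arm, or 262 in total.
- Allowing 5% loss: 262 / 0.95 = 275.8, so 276.

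The stated 262 and 276 are reproduced. Nothing below alters them.

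**Substitute-only collection.** Let q be the probability of the alternative test among women without an OGTT. Then P(event) = (1 − P(OGTT)) × q, and

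RR = [(1 − 0.55) / (1 − 0.37)] × (q_int / q_ctrl) = (0.45 / 0.63) × (q_int / q_ctrl).

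The article gives no value for q, so every q here is an assumption. If q is the same in both arms it cancels:

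| Control OGTT rate | Intervention (+18 points) | RR, equal q | Rise in q needed for RR = 1 |
|---|---|---|---|
| 26% | 44% | 0.56/0.74 = 0.757 | 1.32-fold |
| 37% | 55% | 0.45/0.63 = 0.714 | 1.40-fold |
| 56% | 74% | 0.26/0.44 = 0.591 | 1.69-fold |

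The 26% and 56% limits are the range quoted under Sample size from the South Australian register. Applying the same 18-point gain across that range is an assumption.

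If q differs between arms at 37% v 55%, a 1.2-fold rise gives RR 0.857, a 1.4-fold rise gives 1.00 and a 1.6-fold rise gives 1.143.

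**Collection as defined.** Let s be the probability of a separate alternative test among women who did have an OGTT, with q and s each equal across arms. Then P(event) = (1 − P(OGTT)) × q + P(OGTT) × s. With q = 0.20 assumed:

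- s = 0: 0.090 / 0.126 = 0.714
- s = 0.10: 0.145 / 0.163 = 0.890
- s = 0.20: RR = 1.00
- s = 0.40: 0.310 / 0.274 = 1.131

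The substitute-only form is the special case s = 0. With identical testing behaviour, the way the question is asked can therefore move the risk ratio.

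**Would the distortion reach significance?** Using the uncorrected two-proportion formula with 131 per arm and equal q, the power to detect RR 0.714 is about 9% at q = 0.10, 15% at q = 0.20 and 37% at q = 0.50. The likely harm is a misleading estimate rather than a significant result.

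**Ascertainment.** No arithmetic applies, because the share of women reached only by telephone is not given. Missingness for the secondary outcomes would be the loss on the primary outcome (planned at up to 5%) plus that share.

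**The case against.** The strongest reply is that the questionnaire itself is not shown. One sentence of a condensed article paraphrases its purpose, and the next says that dates and results are requested for these tests in the plural. That fits a form with a separate item for each test. This stands: the form may already collect what the outcomes require. It does not remove the conflict between the two sections as written, and it does not reach the telephone contact or the record check.

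A reader might infer that a successful reminder must force both risk ratios below 1. The documents do not support that. The result needs equal substitution in both arms, or a rise of less than about 1.4-fold. A message about testing for type 2 diabetes could also prompt fasting glucose or HbA1c tests in women who never have the OGTT. Each test has its own substitution rate, so the two ratios need not move together.

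A reader might also infer that the two wordings give opposite results. If the fasting sample inside every OGTT counts as a fasting test, then with q = 0.20 the rates are 0.37 + 0.126 = 49.6% and 0.55 + 0.090 = 64.0%, RR 1.29. That reading is strained. The article lists the OGTT and fasting glucose as separate outcomes and names them as alternatives. It could not apply to HbA1c in any case.

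It is fair to add that overall testing could be derived among questionnaire responders by adding the categories. That holds, but not for women reached only by telephone who report no OGTT. The article also does not say that the call asks about nothing else, and a woman who is telephoned may still return her form.

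**Conclusion.** The definition and the described collection of both secondary outcomes do not match and should be reconciled. If the data are collected as described, the risk ratios are tied to the primary result. They are pulled to 0.71 at the planned rates, and to between 0.76 and 0.59 over control rates of 26% to 56% with an 18-point gain. They stay below 1 unless substitution rises about 1.4-fold under the reminder (1.32 to 1.69 over that range). The size of the pull rests on equal substitution across arms, which is an assumption. The mismatch itself, and the naming of the OGTT alone for telephone contact and confirmation, rest on the text and need no assumption about testing rates. If the call is made as described, women reached only by telephone have no data on either secondary test. The primary outcome and the sample size of 276 are unaffected.

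**What to change.** Bring the two sections into line:

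- Ask every woman whether she had a fasting glucose test and whether she had an HbA1c test by 6 months, with dates, regardless of whether she had an OGTT. Put these questions in both the questionnaire and the telephone script.
- Include both tests in the record and general practitioner check already planned for the OGTT.
- State that the fasting sample taken within an OGTT does not count as a separate fasting glucose test.
- Add a secondary outcome of any postpartum glucose test (OGTT, fasting glucose or HbA1c) by 6 months, so that a shift between tests can be told apart from a change in overall testing.

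If the questionnaire already records each test separately, correcting the description and extending the telephone script and record check is enough for the first two items. The cost is a slightly longer script and check, with no extra participants or procedures. Ranking the any-test outcome above the other secondary outcomes, or reporting the individual tests only descriptively, is a matter of preference and is not needed to resolve the mismatch.

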### Data collection

#### Baseline data collection

Baseline data will be collected to assess the similarity between the two groups in terms of factors that may influence attendance for postpartum oral glucose tolerance testing. At trial entry, information will be collected on demographic characteristics of the participants as well as smoking history, current BMI at booking and previous pregnancy outcomes. With regards to GDM, women will be asked whether or not they were given the opportunity to join the National Diabetes Services Scheme (NDSS) and therefore the National Gestational Diabetes Register, whether they joined, and where they intend to have their postpartum OGTT completed. Data regarding control of GDM (dietary control only or requirement for metformin or insulin), diagnostic OGTT date and results, and complications at birth relating to GDM (requirement for induction, caesarean section, perineal injury, blood loss) will also be collected.

Baseline data relating to the health of the newborn(s) will be collected: singleton or twin, birth order (if twin), gestational age at birth, birth weight (grams), time of birth, gender, Apgar scores, mode of birth (normal vaginal birth, operative vaginal birth, caesarean section), nerve palsy, bone fracture, newborn hypoglycaemia (plasma glucose ≤ 2.0 mmol/L), neonatal intensive care admission, respiratory distress syndrome, neonatal jaundice requiring phototherapy, and death prior to first discharge.

The following information will be collected at hospital discharge: breastfeeding status (given the link between breastfeeding and reduced risk of type 2 DM [32,33], as well as the possible influence that breastfeeding may have on the mother’s ability to attend for oral glucose tolerance testing [34]), mention of GDM in the problem list of the discharge summary and whether or not follow up oral glucose tolerance testing was recommended in the discharge summary.

### Outcome data collection: 6 months postpartum

All women in the study will be asked to complete a questionnaire at 6 months after the birth of the baby either by post or by email (using Survey Monkey), depending on their expressed preference at trial entry, to ascertain whether an OGTT was undertaken within the first 6 months, or whether a fasting blood glucose or glycated haemoglobin (HbA1c) test was used instead. The questionnaire also asks for the date and results of these tests, where known. The date and results of the OGTT will be confirmed using the hospital clinical information system, or by contact with the participant’s general practitioner, where necessary. The questionnaire also examines women’s attitudes towards the OGTT, as well as reasons for not being able to undertake the test, if applicable. Where questionnaires are not returned within 2 weeks, participants will be contacted by telephone, and then again in another 2 weeks if the questionnaires are still not received by the study team. During this telephone contact, participants will be asked whether or not they have completed an OGTT within the six months since they gave birth.

### Sample size

The baseline rate of OGTT uptake used in the sample size calculation for the proposed trial is 37%; this rate is at the lower end of the range in the recent review by Tovar and colleagues (2011) [17]. Using a figure from the lower end of this range is a sound estimate, given that the health centres in the study had reminder systems in place, and that some results came from surveys with moderately low response rates [17]. Data from the South Australian Gestational Diabetes Mellitus Recall Register indicates that the actual rate may be somewhere between 26 and 56 percent [25].

The Stata version 10.0 sample size calculator has been used to calculate the target sample size.

The figures entered were:

▪ baseline uptake of postnatal OGTT 37%

▪ projected 18% absolute improvement to 55% (48% relative increase)

▪ power 80%

▪ significance (two-tailed) 5%

This resulted in a calculation that the study will require 262 women (131 in each arm). With a predicted up to 5% loss to follow up, 276 women will be required.

### Analyses and reporting of results

Baseline characteristics of all randomised women will be compared descriptively between the study groups. Outcome comparisons will be made according to the treatment allocation at randomisation on an ‘intention to treat’ basis. Categorical variables will be reported as risk ratios with corresponding 95% confidence intervals. Continuous outcomes will be reported as mean (and standard deviation) for normally distributed results, or median (interquartile range) for results which are not normally distributed. All model assumptions will be assessed. Statistical significance will be defined at the 0.05 level using a two-sided comparative test.

## Discussion

This randomised controlled trial of a SMS reminder system to improve the rate of attendance for follow up oral glucose tolerance testing in women who have experienced GDM is important given the high, and rising, rate of GDM, and the strong association between GDM and subsequent type 2 DM worldwide. In Australia, this is a particularly timely trial, given the recent establishment of the National Gestational Diabetes Register, the increasingly ubiquitous use of mobile phones, and the decreasing use of postal services (“snail mail”) for communication. Such a reminder system may prove to be a cost-effective measure to reduce future rates of type 2 DM in Australian women, and is therefore of public health as well as obstetric importance. Such a system has the potential to be implemented locally or on a wider scale to improve the health of all women who have experienced GDM.

## Abbreviations

DM: Diabetes mellitus; GDM: Gestational diabetes mellitus; HbA1c: Haemoglobin A1c; OGTT: Oral glucose tolerance test; RCT: Randomised controlled trial; SMS: Short message service.
